### Randomisation and allocation concealment

Following a standard interview at the pre assessment clinic, Patients will be given a written description of the study and information with regard to the exercise class commitment involved. They will also be given stamped addressed envelopes to post back written consent. Following obtainment of written consent random allocation using sequentially numbered envelopes to both groups will be carried out by a third party [name] (LBC) who is not involved in the study. The number sequence will be generated using a computer generated random number table generated by [name] and communicated directly to LBC. Subjects will be randomly allocated either to a functional exercise class from week 12 post op to week 18 or to a control group receiving usual post operative care. Allocation of patients to the treating therapists will be established by e mail contact from LBC to the Physiotherapist’s responsible for conducting the classes. These therapists have been identified previously. Patients will be asked not to discuss their group allocation and all blinded outcome assessment examinations will take place in Our Lady’s Hospital, Navan.

### Physiotherapists

Three experienced physiotherapists one at each site will be trained to supervise the functional exercise classes. Training will comprise a one hour practical workshop and all physiotherapists will be provided with a written illustrated manual of the training workshop.

### Exercise interventions

This functional exercise class is designed to strengthen the hip muscles and incorporates exercises commonly used in clinical practice. It is based on previous work that shows that such an exercise programme improves pain and function [18]. Twelve exercises aimed to strengthen the quadriceps, hamstrings, and hip abductor muscles and improve functional balance will be taught to participants by the Physiotherapist. See Table 1. At the end of the exercise session the physiotherapist will monitor proper form and exercise intensity and will progress the exercises as necessary. Each Physiotherapy session will be 30 minutes in length. Intensity will be determined by the participant’s ability to complete 10 repetitions for a given exercise.

**Table 1 T1:** Functional Hip Exercise circuit

**Exercise**	**Description and progression**
Sit to stand	Sit to stand exercise from chair. Hands used to guide only. Progress with increased repetitions and speed.
Toe raises	Stand straight feet flat on floor, Keep abdomen tight and hold one leg up as you raise on toes as high as possible.
Knee raises	Back straight slowly lift one leg as high as you can and lower to floor raise opposite arms as knee is raised.
Side and back leg raises	Slowly raise leg out to side and then return to start. Repeat with opposite side. Repeat exercise with leg into extension.
Partial knee bends	Stand on both legs. Keep abdomen tight lower towards floor by bending knees to approx 30 degrees. Straighten knees and repeat.
Single knee bends	Stand on one leg, grip floor with toes and slowly lower to approx 30 degrees progress with dumbbells.
One legged standing balance	Use two chairs transfer weight to operated leg and pick other leg up try to balance for 10 seconds. Progress with timed balance.
Advanced one legged balance	As previous but also turn head from side to side.
Pelvic raising/lowering	Stand on operated leg. Stand unsupported not allowing pelvis to drop. Progress by slowly raising and lowering pelvis on the side of the bent knee.

### Follow-up period

The duration of this research project is eighteen weeks from the date of surgery. All patients will complete the WOMAC questionnaire on discharge from hospital at day 5 and all outcome measurements will be repeated at week 12 and again at week 18. The outcome measurement assessments at week 12 and at week 18 will take place in Our Lady’s Hospital in Navan.

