## Methods/design

### Trial design

This will be an assessor blinded two arm randomized controlled trial of a six week involving twelve functional exercise class interventions. Measurements will be taken at day five, week twelve and week eighteen for all subjects. Assessment of adherence to the treatment programme will be assessed with examination of exercise logs completed by clients at each attendance and signed off by the supervising therapist. The classes will be conducted at three sites, Navan, Cavan and Monaghan. The protocol will conform to CONSORT guidelines for reporting non-pharmalogical interventions and has been registered with clinical trials.gov prior to study commencement.

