### Procedure

Preliminary screening will be carried out at the pre-assessment clinic by the principal investigator (BM). Following a standard interview process patients will be given a written description of the study and information with regard to the exercise class commitment involved. A screening record will be kept to document criteria eliminating those deemed to be ineligible. All patients will all be assessed using the WOMAC questionnaire on day 5 prior to discharge and they will be randomized to one of two treatment groups. The functional exercise intervention begins at week 12 and all patients will complete the Primary and Secondary outcome assessments at this point. All assessments are repeated for both groups at week 18. Patients allocated to the functional exercise class will attend a six week functional exercise programme twice weekly from week 12 to week 18. The control group will receive the standard usual post surgery care as outlined in the patients’ information booklet given to all patients on admission. This care is given to all patients post surgery by the Physiotherapist working on the ward. This study is one comparing usual treatment with an intervention of functional exercise. All patients randomised to the usual care group will be offered the chance to attend the exercise group at week 18 post evaluation.

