### Primary outcome measurements

#### Western Ontario and Mc master universities osteoarthritis index (WOMAC) likert version 3.1

This is a multidimensional, self administered disease specific standardized instrument which is proven to be reliable and valid within this client group [19]. The outcomes will be completed during face to face contact with the assessor (BM) in the Physiotherapy department prior to hospital discharge on day five and repeated at week 12 and week 20. The questionnaire consists of 24 questions regarding pain (scored 0–20) stiffness (scored 0–8) and physical function (scored 0–68). For each division a score is calculated the range of scores is from 0–98 with higher scores indicating a lower health status. Minimal perceptible clinical improvement on the WOMAC questionnaire has been established in the literature at −10.4 with the standard deviation of scores on the instrument at 13.6 [20].

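### The primary questionnaire has no stated route other than a visit to the assessor, so a missed final visit loses an outcome that the analysis then drops

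*Protocol article*

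**What the plan says.** The WOMAC section of the protocol article describes the primary instrument as follows: "This is a multidimensional, self administered disease specific standardized instrument". On collection it says: "The outcomes will be completed during face to face contact with the assessor". That sentence places the first completion in the Physiotherapy department before discharge on day five, then has it repeated at week 12 and week 20.

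Two sections fix the place of the later assessments. Follow-up period says: "The outcome measurement assessments at week 12 and at week 18 will take place in Our Lady’s Hospital in Navan". Randomisation and allocation concealment says that "all blinded outcome assessment examinations will take place in Our Lady’s Hospital, Navan". Under Trial design, the exercise sites are wider: "The classes will be conducted at three sites, Navan, Cavan and Monaghan".

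Procedure gives the usual-care arm a later offer: "All patients randomised to the usual care group will be offered the chance to attend the exercise group at week 18 post evaluation". It states no matching offer to the exercise arm.

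Statistical analysis promises intention to treat for everyone randomised, whatever treatment they received. It then takes missing primary outcomes as missing at random and omits them from the primary analysis, which consists of t tests at 12 and 18 weeks. Sample size allows one overall attrition figure of 10%.

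Post is already used in the trial, for consent: "They will also be given stamped addressed envelopes to post back written consent".

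**The concern.** A questionnaire that patients fill in themselves does not need a clinic visit, but the stated plan ties it to one. A patient who stops the classes, or for whom Navan is a long journey, can miss the visit, and the primary outcome is lost with it.

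The missing-data rule then removes that patient from the comparison. A t test on those observed at week 18 uses no earlier score. Assuming missing at random therefore does not protect it: if loss depends on how patients were doing at week 12, and does so differently by arm, the difference in means can be biased even when that assumption is true. With this analysis, obtaining the outcome is the main safeguard of the intention-to-treat claim.

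There are reasons to think loss might differ between arms. Only the exercise arm has a programme to stop, and stopping may be related to pain or function, which the WOMAC measures. Only usual care has the class still to come after the evaluation. What is at stake is mainly bias in the primary comparison, more than power.

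**Working it through.** **1. The plan's own figure.** Inputs from Sample size: difference 10.4, SD 13.6, two-sided 5%, power 80%.

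- n per arm = 2 × (1.96 + 0.842)² × (13.6 / 10.4)² = 2 × 7.85 × 1.710 = 26.8, so 27 per arm and 54 in total, as stated. The exact t-test calculation gives 27.8, so 28 per arm.
- With 10% attrition: 54 / 0.90 = 60, as stated. The trial plans 70, or 35 per arm.

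**2. Does loss threaten power?** Noncentral t, same difference and SD, starting from 35 per arm. The loss rates are assumed.

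| Loss, exercise / usual care | Patients analysed | Power |
|---|---|---|
| 0% / 0% | 35 / 35 | 88% |
| 10% / 10% | 32 / 32 | 85% |
| 20% / 5% | 28 / 33 | 83% |
| 30% / 5% | 24 / 33 | 80% |
| 40% / 5% | 21 / 33 | 77% |

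Power stays near 80% up to about 30% loss in the exercise arm. The issue is bias.

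**3. Size of a possible bias.** If a share m of one arm is missing, and those patients would have scored k points worse than the patients observed in that arm, the observed mean is too favourable by m × k.

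Assumptions: m is 10% to 20% in one arm, with no comparable selective loss in the other; k is 0.5 to 1 SD, with SD 13.6. The 20% corresponds to the planned attrition (10% of 70 = 7 patients) falling wholly in one arm: 7 / 35 = 20%.

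| m | k | Bias, points | Share of 10.4 |
|---|---|---|---|
| 10% | 6.8 | 0.10 × 6.8 = 0.68 | 6.5% |
| 10% | 13.6 | 0.10 × 13.6 = 1.36 | 13.1% |
| 20% | 6.8 | 0.20 × 6.8 = 1.36 | 13.1% |
| 20% | 13.6 | 0.20 × 13.6 = 2.72 | 26.2% |

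**4. Effect on the test.** Take m = 20% and k = 10.4 in the exercise arm, with 28 and 33 patients analysed and no true effect. The bias is 0.20 × 10.4 = 2.08 points. The standard error is 13.6 × √(1/28 + 1/33) = 3.49. The shift is 2.08 / 3.49 = 0.60 standard errors, and the two-sided 5% test rejects about 9% of the time (normal approximation).

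**5. What these figures are not.** m and k are not in the article. The results are the total bias from such loss, not the part a posted form would remove.

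**6. The final time point.** Any fallback needs one agreed date, and the article gives several:

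- Follow-up period: week 18 for all outcomes.
- Table 2: week 18 for pain and physical function, week 15 for stiffness, week 20 for the VAS.
- WOMAC section: week 20.

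**The case against.** **A condensed article may leave non-attender procedures to the full protocol.** This stands in part. The sections cited say where and how scheduled assessments take place, and none says that a missed visit ends collection. But the mode, the place and the missing-data rule are all stated, and the point is how these stated choices work together.

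**Face-to-face completion is tied to day five.** The sentence does name the pre-discharge assessment, but it continues with the repeats, and the later assessments are separately placed in Navan. Reading it as the route for every time point is reasonable.

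**One site and one mode are defensible.** This stands. The walk test, Berg score and ultrasound need a visit, and a single mode keeps the WOMAC comparable. It supports Navan as the default, not the absence of a fallback.

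**Follow-up after stopping is already implied.** Both arms are to be reassessed at week 18, and the intention-to-treat statement covers patients who stop. The intention is there; a route for those who do not come is not stated.

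**A reader might infer that exercise patients will be lost more often and that the result will favour exercise.** The article does not support this. Attrition is one figure, not split by arm. Both arms travel to Navan and were recruited there. Up to twelve supervised contacts could improve retention in the exercise arm, and patients who stop because they feel well would reverse the sign.

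**A reader might also infer that usual-care patients are rewarded for attending.** The offer of the class is timed after the evaluation; it is not stated to depend on attending it.

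**Posting will not reach everyone.** This stands. Patients too unwell or disengaged to travel may not return a form either.

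**Conclusion.** The point holds as a weakness in outcome collection. A self-administered primary questionnaire is tied to a visit, and those without a visit are dropped from an unadjusted comparison presented as intention to treat. Some of that loss is avoidable for the WOMAC, and likewise for the SF-36 and VAS. It is not avoidable this way for the walk test, Berg score or ultrasound.

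Uneven loss between arms is a credible risk whose size and direction the article does not settle. On the stated assumptions the total bias would be 0.7 to 2.7 points, or 7% to 26% of the target difference. The upper end needs all seven planned losses in one arm and each missing patient a full SD worse. The part recoverable by post is smaller and cannot be quantified from the article.

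The change should be made because it is cheap and reduces missing primary outcomes whichever arm loses more. Confidence is medium.

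**What to change.** First reconcile the final time points for the WOMAC, its stiffness subscale and the VAS across Follow-up period, Table 2 and the WOMAC section.

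Then add to Follow-up period and the WOMAC section:

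- The final WOMAC, SF-36 and VAS are sought from every randomised patient in both arms, whether or not they attended or stopped the classes.
- A patient who does not attend the Navan visit is sent the forms with a stamped addressed envelope and one reminder. Usual-care patients complete them before starting the class.
- The mode and date of completion are recorded.
- Posted responses enter the primary intention-to-treat analysis, with a sensitivity analysis restricted to face-to-face completions.

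The cost is postage and a short amendment. The downside is that a few forms are completed without the assessor present, which the recorded mode and the sensitivity analysis allow to be examined. The walk test, Berg score and ultrasound would still be missing for those patients.

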### Measurements

Baseline descriptive data will be obtained by questionnaire and will include age, sex, weight, height, medication use and previous health problems. A summary of all measurements is included in Table 2

**Table 2 T2:** Summary of outcomes to be collected

**Primary Outcome Measurement**	**Data Collection Instrument**	**Collection times in weeks**
Pain	Pain Subscale of the WOMAC osteoarthritis index 3.1 Likert Version	Day 5 Week 12 Week 18
Self reported Physical Function	Physical Function subscale of the WOMAC osteoarthritis index 3.1 Likert Version	Day 5 Week 12 Week 18
Self reported Stiffness	Stiffness Function subscale of the WOMAC osteoarthritis index 3.1 Likert Version	Day 5 Week 12 Week 15
**Secondary Outcome measurement**		
Real time ultrasound of the Gluteus Medius Muscle	Cross sectional area measurement	Week 12 Week 18
6 Minute Walk Test	Functional Performance	Week 12 and Week 18
Short Form SF-36	Self reported measurement of health Status and quality of life	Week 12 and Week 18
Berg Balance Score	Functional balance assessment scale	Week 12 and Week 18
Visual Analogue Scale	Average overall pain in past week 100mm VAS	Day 5, Week 12, and Week 20

### Primary outcome measurements

#### Western Ontario and Mc master universities osteoarthritis index (WOMAC) likert version 3.1

This is a multidimensional, self administered disease specific standardized instrument which is proven to be reliable and valid within this client group [19]. The outcomes will be completed during face to face contact with the assessor (BM) in the Physiotherapy department prior to hospital discharge on day five and repeated at week 12 and week 20. The questionnaire consists of 24 questions regarding pain (scored 0–20) stiffness (scored 0–8) and physical function (scored 0–68). For each division a score is calculated the range of scores is from 0–98 with higher scores indicating a lower health status. Minimal perceptible clinical improvement on the WOMAC questionnaire has been established in the literature at −10.4 with the standard deviation of scores on the instrument at 13.6 [20].

#### Secondary outcome measurements

##### Real time ultrasound imaging of the gluteus medius muscles

Real time ultrasound of the gluteus medius will establish the size of the muscle pre and post the functional exercise class. Measurement on day five is not possible due to wound dressing and patient positioning issues. Patients will be scanned by the radiologist at week 12 and the scan will be repeated at week 18. Intra therapy reliability testing will be carried out prior to scanning and the radiologist will be blinded to group allocation. Repeated measurement at week 18 will allow for comparison of both groups with and without intervention. Exploratory analysis on a subgroup of patients using real timed ultrasound to assess the size of gluteus medius in the non affected side will also carried out. This subgroup will be randomly selected from the main group following initial randomisation. It is planned to compare the size of the gluteus medius in the non affected side with the affected side at week 12 and again at week 18.

##### 6 Minute walk test

This is a reliable and valid test of physical function in this client group and has been shown to be responsive to detecting deterioration and improvement in the early post operative period [21]. It will be completed by the principal investigator (BM) who will remain blind to group allocation.

##### Short form SF-36

This is a well recognized and valid self reported questionnaire that measures health status and quality of life [22]. It will be completed in the presence of the principal investigator who will remain blinded to group allocation.

##### Berg balance score

This assessment scale of ability to maintain balance both statically and whilst performing various functional tasks will be completed by the blinded principal investigator (BM) at week 12 and repeated for all patients at week 18. It has been demonstrated to be valid and reliable in older adults [23].

##### Visual analogue scale

This 100mm scale with descriptors at either end of the scale of “no pain”, and “worst possible pain” allows for self assessment of levels of pain at any specific time. It has been demonstrated to be reliable in the osteoarthritic client group [24].

#### Sample size

The power calculations were based on the physical function subscale of the WOMAC questionnaire. The minimal clinical difference on the WOMAC questionnaire has been established in the literature at −10.4 with the standard deviation of scores on the instrument at 13.6 [20]. The sample size was then calculated requiring a power of 80% in a two tailed test with a significance level of .05. The effect size was calculated at 10.4/13.6. It was .764 or a mod/large effect size. The sample size required was then calculated at 27 patients in each group or 54 in total. This would increase to 60 patients in total allowing for 10% attrition.

Consideration of the power calculations based on both the Berg balance score and the SF36 short form health survey, similar numbers are required. Using minimal detectable change scores and standard deviations from the literature [25] sample sizes at 80% power and .05 significance in a two tailed test were calculated at 70 subjects in total for the Berg Balance score and 54 subjects for the SF36 respectively. Therefore 70 subjects in total or 35 in each group would allow for 10% attrition for all outcome measurement tools.

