**Methods/design:**

This will be a single blind multi centre randomized control trial with two arms. Seventy subjects post primary total hip arthroplasty will be randomized into either an experimental group (n=35), or to a control group (n=35). The experimental group will attend a functional exercise class twice weekly for a six week period from week 12 to week 18 post surgery. The functional exercise group will follow a circuit based functional exercise class supervised by a chartered Physiotherapist. The control group will receive usual care. The principal investigator (BM) will perform blinded outcome assessments on all patients using validated measures for pain, stiffness, and function using the Western Ontario and Mc Master Universities Osteoarthritis index (WOMAC). This is the primary outcome measurement tool. Secondary outcome measurements include Quality of life (SF-36), 6 min walk test, Visual Analogue Scale, and the Berg Balance score. The WOMAC score will be collated on day five post surgery and repeated at week twelve and week eighteen. All other measurements will be taken at week 12 and repeated at week eighteen. In addition a blinded radiologist will measure gluteus medius cross sectional area using real time ultrasound for all subjects at week 12 and at week 18 to determine if the functional exercise programme has any effect on muscle size.

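### Berg and SF-36 are powered on a minimal detectable change, not shown to be a worthwhile between-arm difference, and Berg's 70 leaves no room for the 10% attrition it is said to cover

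*Protocol article*

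**What the plan says.** The Sample size section makes three calculations, all for 80% power and a two-sided test at .05.

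- **WOMAC physical function (primary).** The target is described as a clinical threshold: "The minimal clinical difference on the WOMAC questionnaire has been established in the literature", at 10.4 points with an SD of 13.6. Then "The effect size was calculated at 10.4/13.6", or .764. This gives 27 per arm and 54 in total, raised to 60 for 10% attrition.
- **Berg and SF-36 (secondary).** The kind of target changes: "Using minimal detectable change scores and standard deviations from the literature [25] sample sizes at 80% power". The totals "were calculated at 70 subjects in total for the Berg Balance score and 54 subjects for the SF36 respectively". No MDC or SD is printed for either scale.
- **Final size.** "Therefore 70 subjects in total or 35 in each group would allow for 10% attrition for all outcome measurement tools".

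The abstract (Methods/design) carries the number forward: "Seventy subjects post primary total hip arthroplasty will be randomized".

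**The concern.** There are two linked problems.

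**The target.** An MDC is the smallest change in one person's score that exceeds that person's measurement error. A two-arm comparison concerns the difference between two means, in which individual error is averaged over patients. An MDC may lie below, at or above the mean difference that patients or clinicians would value. To use it as the target of a power calculation, one has to argue that it is also a worthwhile mean difference. The section makes no such argument, although for WOMAC it does start from a threshold described as clinical.

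**The attrition.** 70 appears first as what Berg requires and then as a number that already covers 10% loss for every instrument. Both hold for Berg only if its 70 was already inflated, and the section does not say that it was.

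At stake are the stated reason for enrolling 70 rather than the 60 that WOMAC needs, and the statement that balance and quality of life, both named in the Secondary hypotheses, are adequately powered.

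**Working it through.** **Inputs, all from the Sample size section.** WOMAC 10.4 and 13.6; two-sided .05; 80% power; totals of 54 (WOMAC), 70 (Berg) and 54 (SF-36); final size 70 in two equal arms; 10% attrition.

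**1. Reproduce the plan's own figure.** Normal approximation: n per arm = 2(1.960 + 0.8416)² / d² = 15.70 / d². With d = 10.4/13.6 = 0.7647, n = 15.70 / 0.5848 = 26.8, so 27 per arm and 54 in total, as stated (the t-based calculation gives 28). Attrition: 54 / 0.9 = 60, also as stated. The WOMAC line is sound on its own inputs.

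**2. Back-solve the Berg and SF-36 targets.** Their totals cannot be reproduced, because neither the MDC nor the SD is given. Inverting the formula gives d = √(15.70 / n).

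| Scale | n per arm | Implied d, normal | Implied d, t test |
|---|---|---|---|
| Berg | 35 | 0.67 | 0.68 |
| SF-36 | 27 | 0.76 | 0.78 |

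**3. Which scale sets the size.** After 10% attrition, WOMAC needs 60 and SF-36 needs 54 / 0.9 = 60. Only Berg gives 70.

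**4. Berg after attrition.** 70 × 0.9 = 63 completers, on average 31.5 per arm.

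- Normal approximation: 0.6697 × √(31.5/2) − 1.960 = 2.658 − 1.960 = 0.698, and Φ(0.698) = 0.76.
- t-based power at d = 0.679: 75.6% (74.9% with 31 per arm, 76.3% with 32).
- Keeping 80% after 10% loss would take 70 / 0.9 = 77.8, so 78 randomised.

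**5. The other outcomes with 63 completers (t-based).** WOMAC at 10.4/13.6 has 84.8% power. SF-36 at its implied target has 85.9%. The smallest difference with 80% power is 0.72 SD.

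**6. Why the direction is open.** No worthwhile difference for Berg or SF-36 is given, so a range has to be assumed. The table shows power with all 35 per arm (t-based) if the worthwhile difference is a given multiple of the target used.

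| Worthwhile difference ÷ target used | Berg | SF-36 |
|---|---|---|
| 0.5 | 29% | 36% |
| 0.75 | 56% | 67% |
| 1.0 | 80% | 89% |
| 1.25 | 94% | 98% |

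Nothing in the document says which row applies.

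**The case against.** **These are secondary outcomes.** A trial need not be powered for them, and the step only raised the size from 60 to 70, which helps the primary outcome. This stands and limits the weight of the point. However, the section chooses to claim 80% power for these scales and takes its final number from one of them, so the claim should be supportable.

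**Berg's 70 may already include attrition.** 63 / 0.9 is exactly 70. On that reading the implied target is 0.72 SD, and the shortfall in step 4 disappears. Against it, the sentence presents 70 and 54 as results of the same kind, and the 54 for SF-36 equals WOMAC's figure before attrition. An odd total of 63 would also be unusual for two equal arms. The section still needs to say which is meant.

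**The WOMAC 10.4 may be a patient-level threshold too.** The Primary outcome measurements section calls it a perceptible improvement. That is fair as far as it goes, but the figure is printed and presented as clinically meaningful, which the Berg and SF-36 targets are not.

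**Stronger readings that a reader might infer, and that the document does not support:**

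- *The 80% power is for a difference that is not worthwhile, or balance is underpowered.* Without the MDCs, SDs or important differences, neither follows.
- *Both secondary calculations set the trial size.* SF-36 gives 54; only Berg gives 70.
- *The implied effect reflects instrument reliability alone, so a noisier scale would need fewer patients.* This requires a particular form of MDC computed from the same SD used as the divisor. The section states neither.
- *Non-significant Berg or SF-36 results will be taken as evidence of no benefit.* The Statistical analysis section gives no such rule.

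**Conclusion.** The point holds in limited form. The Sample size section uses an individual measurement-error bound as the between-arm target for Berg and SF-36 without justification, so the 80% power for those scales is not shown to be for a worthwhile difference. The direction of any error is unknown.

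Separately, 70 cannot be Berg's requirement before attrition and also cover 10% loss. Power at the implied target is then about 76%. That figure assumes a two-sample t test, equal arms, 10% loss spread evenly, and a 70 that was not already inflated.

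The primary WOMAC calculation reproduces and is not affected. This is a correction to a stated justification for secondary outcomes. It does not challenge the trial's size.

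**What to change.** Reword the end of the Sample size section:

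- Justify 70 on WOMAC physical function: 63 completers give about 85% power for 10.4/13.6.
- Replace the Berg and SF-36 power claim with a statement that 63 completers give 80% power for a between-arm difference of about 0.72 SD, and that this is not claimed to be the smallest worthwhile difference on either scale.
- Remove the statement that 70 covers 10% attrition for every instrument.
- State that Berg and SF-36 will be reported as between-arm differences with 95% confidence intervals.

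The cost is one reworded paragraph and one reporting sentence, with no extra patients, visits or data. The downside is that the stated power for the secondary outcomes becomes less favourable.

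### Seventy patients do not allow for 10% attrition on the Berg Balance score, because the Berg calculation already needs all 70

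*Protocol article*

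**What the plan says.** All the figures are in the Sample size section of the protocol article.

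- **WOMAC (primary).** The calculation was done "requiring a power of 80% in a two tailed test with a significance level of .05". On the effect size: "The effect size was calculated at 10.4/13.6". The result: "The sample size required was then calculated at 27 patients in each group or 54 in total". Attrition is then added as a separate step: "This would increase to 60 patients in total allowing for 10% attrition".
- **Berg and SF-36 (secondary).** With inputs drawn from a cited source, and for the same power and two-sided significance level, the article reports these requirements: "70 subjects in total for the Berg Balance score and 54 subjects for the SF36 respectively". No attrition step is described for either.
- **Conclusion.** "Therefore 70 subjects in total or 35 in each group would allow for 10% attrition for all outcome measurement tools".

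The Abstract gives the same enrolment of 70, 35 per arm.

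**The concern.** The section first derives a number from power and then, where it allows for loss, enlarges it and says so. It does this for the WOMAC. For Berg it gives a power-based 70 and adopts 70 as the enrolment, so nothing is left over for dropouts. The closing sentence nevertheless claims a 10% allowance for every tool.

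Berg is a secondary outcome, but balance is named in the secondary hypotheses, and Berg is the tool that raises the sample from 60 to 70. The attrition claim therefore fails for the outcome that sets the trial's size. A null Berg result would be read as coming from a comparison that kept 80% power under the planned loss, when it did not.

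**Working it through.** **Inputs (all from the Sample size section).** Two-sided alpha 0.05; power 80%; 1:1 allocation; WOMAC difference 10.4 and SD 13.6; 10% attrition; Berg 70, SF-36 54 and planned enrolment 70 in total.

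**1. Reproduce the WOMAC figures.**
- d = 10.4 / 13.6 = 0.765 (printed as .764).
- Normal approximation: n per arm = 2 × (1.960 + 0.842)² / 0.765² = 26.8, rounded up to 27, so 54 in total. This matches.
- A t-based calculation gives 27.8, so 28 per arm and 56 in total, which is close enough.
- Attrition: 54 / (1 − 0.10) = 60. This matches, so dividing by 0.9 reproduces the article's attrition step.

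**2. Apply the same step to Berg.**
- 70 / 0.9 = 77.8, rounded up to 78 (39 per arm).
- Multiplying by 1.10 instead gives 77, which is also 78 once split into equal arms.
- The planned 70 is therefore 8 below what the stated allowance requires.

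**3. Completers if 70 are randomised and 10% are lost.**
- 70 × 0.9 = 63, or about 31 and 32 per arm.
- Berg: 63 against 70 needed, short by 7.
- WOMAC and SF-36: 63 against 54 needed, so both are covered. They could bear a loss of up to 1 − 54/70 = 22.9%.

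**4. Size of the Berg shortfall.** The article prints neither the Berg difference nor its SD, so the effect size has to be back-solved on the assumption that 35 per arm gives exactly 80% power.
- Normal approximation: d = (1.960 + 0.842) × √(2/35) = 0.67. The two-sample t-test gives 0.68.
- Power at 31.5 per arm: 75.6% (t) or 75.7% (normal). At 31 per arm it is 74.9% and at 32 it is 76.3% (t).
- If 80% was already reached at 34 per arm and 35 includes some rounding, power at 63 completers is 76.8%.
- Type II error is therefore about 24% rather than 20%.

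**5. WOMAC power with 63 completers.** With d = 0.765 and 31.5 per arm, the t-test gives 84.8%.

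**The case against.** The strongest reply is that the Berg 70 may already include attrition. The article does not label it as before or after loss and prints no Berg inputs. The arithmetic can be made to fit: 31 evaluable per arm gives 31 / 0.9 = 34.4, rounded up to 35 per arm and 70 in total. The closing sentence would then be correct. The match between the SF-36 figure and the uninflated WOMAC figure, both 54, could be coincidence, since the two rest on different cited sources.

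This reading is possible, but no text supports it. The article gives 70 and 54 in one clause as sizes calculated for 80% power, and it states the attrition step openly in the one place it uses it. Reading 70 as uninflated is the natural reading.

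Two parts of the reply do stand. First, the 76% depends on back-solving from 70, so it is conditional until the Berg inputs are shown. Second, the consequence is small: about 4 points of power, on one of several secondary outcomes, and only if loss reaches 10%. The primary comparison is not affected.

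**Conclusion.** The concern holds. As written, the claim that 70 patients allow 10% attrition for every tool is wrong for the Berg Balance score and right for the WOMAC and SF-36. The gap is 7 completers (63 against 70), or 8 randomised patients (70 against 78). Berg power under the planned loss is about 76%, with a range of about 75% to 77% over the arm split, rounding, and normal or t calculation. This assumes that 70 is the pre-attrition requirement and that dropouts leave the Berg analysis. The primary WOMAC calculation keeps its margin at about 85%, so the error misstates a property of the design without undermining the main comparison.

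**What to change.** Keep 70 and replace the closing sentence of the Sample size section with, for example:

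> With 70 randomised and 10% attrition (63 completers), power is about 85% for a WOMAC effect size of 0.764 and about 76% for the Berg target. The 10% allowance holds for the WOMAC and SF-36 but not for the Berg Balance score.

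Before using the Berg figure, the authors should state the Berg difference, SD and pre-attrition number and confirm that 70 is uninflated. If 70 already includes attrition, they should print the smaller evaluable number instead; the present conclusion would then follow.

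The cost is one or two sentences and a slightly less favourable Berg figure. Enrolment, design and analysis do not change. Keeping 80% for Berg under 10% loss would instead mean randomising 78, which is not needed for the primary outcome.
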